**Methods/design:**

The Long-term Effects of high-doSe pitavaStatin on Diabetogenicity in comparison with atorvastatin in patients with Metabolic syndrome (LESS-DM) trial is a prospective, randomized, open-label, active control clinical trial of patients with MetS. We plan to randomize 500 patients with MetS (1:1) to receive high-dose pitavastatin (4 mg) or atorvastatin (20 mg) daily for 24 months. The primary endpoint will be the change in hemoglobin A1c after statin treatment. Secondary endpoints will include the following: (1) changes in biochemical markers, including insulin, C-peptide, homeostasis model assessment of insulin resistance and insulin secretion, and adiponectin; (2) changes in imaging parameters, including carotid elasticity metrics and indices of cardiac function; and (3) the incidence of clinical events, including new-onset diabetes and cardiovascular disease.

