### Study participants

We will recruit from patients with MetS of both genders, aged 21 years or older, and who are candidates for statin therapy for prevention against CVD who visit outpatient clinics. These patients with MetS will be eligible only when they have no evidence of diabetes at baseline. Diabetes mellitus will be diagnosed as a random plasma glucose level ≥ 200 mg/dl along with classic symptoms of hyperglycemia, fasting plasma glucose level ≥ 126 mg/dl, 2-h postprandial plasma glucose level ≥ 200 mg/dl, and/or hemoglobin A1c ≥ 6.5%, or if a patient is taking medication for diabetes [14]. MetS will be defined according to the National Cholesterol Education Program Adult Treatment Panel III criteria [15]. The definition for anthropometric cutoff points of abdominal obesity will be based on the International Obesity Task Force criteria for the Asia-Pacific population [16]. The indication for statin therapy will be defined on the basis of the current guidelines [1]. Subjects fulfilling at least one of the following exclusion criteria will not be eligible for this study: (1) history of acute coronary syndrome or cerebrovascular disease in the past 2 months; (2) history of statin exposure within the past 1 month; (3) any anticipated change in statin regimen; (4) active malignancy; (5) cholestasis (serum total bilirubin > 3 mg/dl) or active liver disease (serum alanine transaminase > 200 IU/L); (6) chronic renal failure (serum creatinine > 2 mg/dl); (7) failure to obtain informed consent; (8) difficulty in completing follow-up; (9) concomitant use of medications affecting glucose metabolism, such as steroids and atypical antipsychotics; (10) known allergy to statins; and (11) any contraindication to statin therapy, including pregnancy/potential pregnancy, breastfeeding, cyclosporine use, myopathy, or genetic disorders.

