### Statistical analyses

The statistical analyses will be performed on both intention-to-treat and per-protocol bases. The intention-to-treat analyses will include all randomized participants who provide written informed consent, regardless of whether the study treatment is administered correctly. The per-protocol analyses will include all study participants who complete the trial with an adequate administration of the study drug (≥70% of the planned doses) and without any major protocol violations. Major protocol violations include inappropriate enrollment, the use of a prohibited concomitant medication, a violation of the dose or schedule of drug administration, or any other violation considered to be a major violation. The main analyses will be performed on an intention-to-treat basis.

The values will be expressed as the mean ± SD or median (IQR), as appropriate. Comparisons of continuous and categorical data will be made by Student’s *t* test and the chi-square test, respectively. The difference in changes between the groups will be analyzed using both Student’s *t* test and analysis of covariance to adjust for the baseline values. Two-sided *p* values < 0.05 will be considered statistically significant. All analyses will be performed using IBM SPSS version 22.0 software (IBM, Armonk, NY, USA).

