### Strengths and weaknesses

To date, there have been few head-to-head trials comparing the effects of different statins on glucose metabolism. Therefore, our study has an advantage in this respect because we will directly compare the effect of pitavastatin with that of atorvastatin, one of the most widely used statins clinically, on glucose metabolism and NOD. Another strength of this study is the provision of information regarding the impact of statins on adiponectin, which may give insight into the potential mechanisms underlying the difference in diabetogenic properties according to the statin type. This study also has an advantage in that it will include analyses of the effects of statin therapy on imaging surrogate markers, such as carotid elasticity metrics and echocardiographic parameters. On one hand, the results of these analyses will address the question whether the use of less-diabetogenic statin types has more beneficial effects on vascular and cardiac functions in patients at high risk for diabetes. On the other hand, the major limitation of our study is that the sample size is relatively small to detect differences in clinical outcomes, such as NOD or cardiovascular events, between the groups. To mitigate this limitation, we plan to use imaging surrogate endpoints, which may allow for a smaller sample size and a shorter study duration than clinical endpoints and thereby enable the assessment of the potential benefits of pitavastatin on cardiovascular outcomes. However, we should acknowledge that this approach based on imaging surrogate indicators cannot be fully applied to NOD. Another limitation is a lack of power to perform reliable subgroup analyses based on relevant variables. For example, given that age is a major risk factor for diabetes, subgroup analyses looking at narrower age ranges will provide additional valuable information on potential age group differences in the risk of statin-induced diabetes. Large clinical trials need to be conducted to determine which age group is the most susceptible for developing statin-induced diabetes or most benefits from the use of less-diabetogenic statins. With regard to gender, although there are no direct data on gender differences in the association between statin use and NOD, some previous studies suggested that diabetogenic potential of statins might be gender-specific by demonstrating that the baseline level of adiponectin and the effect of statins on adiponectin could be different between males and females [56, 57]. Further trials with adequate numbers of males and females are required to be able to answer the diabetogenic potential of statins based on gender differences. We should also acknowledge that the influence of previous statin use on the study endpoints cannot be completely excluded, even though we will exclude patients with a history of statin exposure within 1 month before enrollment and thus will perform stratified randomization according to the previous use of statins. Finally, patients receiving some antihypertensive agents with potential to affect glucose metabolism, such as thiazide-type diuretics, β-blockers, angiotensin-converting enzyme inhibitors, and angiotensin receptor blockers, which may be important covariates, can be included in our study [58]. If these covariates are not evenly distributed between study groups despite randomization, we will perform adjusted analysis in this randomized controlled trial to correct for the imbalances in covariates.

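### New-onset diabetes falls under an unadjusted chi-square test although baseline HbA1c is measured in everyone; the test is valid, but adjustment would add a few points of power at almost no cost

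*Protocol article*

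**What the plan says.** Under Statistical analyses, the protocol article gives one rule by type of variable: "Comparisons of continuous and categorical data will be made by Student’s *t* test and the chi-square test, respectively". Between-group differences in changes get a t test and also "analysis of covariance to adjust for the baseline values". Nothing comparable is given for a binary outcome.

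NOD is such an outcome. The abstract lists among the secondary endpoints "the incidence of clinical events, including new-onset diabetes and cardiovascular disease". Under Study participants, diabetes is defined by several routes, among them "fasting plasma glucose level ≥ 126 mg/dl, 2-h postprandial plasma glucose level ≥ 200 mg/dl, and/or hemoglobin A1c ≥ 6.5" (the last figure in percent). Current drug treatment of diabetes also counts, and anyone meeting the definition at entry is excluded. Every participant therefore starts below 6.5%. Table 1 schedules HbA1c and fasting glucose at baseline, 12 and 24 months. Randomisation is stratified by gender and previous statin use, not by glycaemia.

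Under Strengths and weaknesses, the authors give as the main limitation that "the sample size is relatively small to detect differences in clinical outcomes, such as NOD or cardiovascular events, between the groups". The same section holds the only other reference to adjustment, introduced for antihypertensive drugs: "If these covariates are not evenly distributed between study groups despite randomization, we will perform adjusted analysis".

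**The concern.** NOD by HbA1c is a threshold crossing of a variable whose starting value is known. A participant who enters at 6.4% and one who enters at 5.2% have very different chances of reaching 6.5%, yet the chi-square test treats them alike. The plan accepts the case for baseline adjustment when HbA1c is analysed as a change, and does not carry it over when HbA1c is cut at 6.5%.

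The conditional adjustment does not fill this gap. It does not name baseline HbA1c, it is triggered by observed imbalance, and a decision of that kind made after the data are seen in an open-label trial is weaker than one fixed beforehand.

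What is at stake is the precision of the clinical endpoint closest to the trial's question, one for which the authors already expect too little power.

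**Working it through.** **1. Inputs from the protocol article.** Difference in HbA1c change 0.2 points; variability 0.5, called a variance; 95% power, two-sided 5%; 10% dropout; 250 per group, so 250 × 0.9 = 225 evaluable per arm. No NOD rate, baseline HbA1c distribution or baseline-to-follow-up relation is given, so these must be assumed.

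**2. The plan's own figure.** With n per arm = 2(z₀.₉₇₅ + z_power)² × variance / difference²:
- Variance 0.5, 95% power: 2 × (1.960 + 1.645)² × 0.5 / 0.04 = 325; 325 / 0.9 gives 362.
- SD 0.5 (variance 0.25), 95% power: 163; 163 / 0.9 gives 182.
- Variance 0.5, 85% power: 2 × (1.960 + 1.036)² × 0.5 / 0.04 = 225; 225 / 0.9 = 250.

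The stated 250 does not follow from the stated inputs at 95% power. That is a separate matter. Here it means that both readings of 0.5 have to be carried: SD of change 0.707 (variance 0.5) and SD 0.5.

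**3. Unadjusted power for NOD at 225 per arm.** Power = Φ[(Δ − 1.96 × SE₀) / SE₁], with SE₀ from the pooled rate and SE₁ from the separate rates. For assumed rates of 12% and 20%: Δ = 0.08, SE₀ = √(2 × 0.16 × 0.84 / 225) = 0.0346, SE₁ = √[(0.12 × 0.88 + 0.20 × 0.80) / 225] = 0.0344, and power = 64%. Other assumed pairs: 3% v 6%, 34%; 5% v 10%, 52%; 8% v 12%, 29%; 10% v 15%, 36%. This agrees with the authors' own admission.

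**4. Gain from adjustment.** Simulation, 3,000 runs per scenario, 225 per arm. Baseline HbA1c is normal, truncated below 6.5%. Follow-up = mean + slope × (baseline − mean) + 0.2 × arm + residual, with the residual scaled to give the chosen SD of change. NOD is month-24 HbA1c of at least 6.5%. The chi-square test is compared with the standardised risk difference from a logistic regression on arm and baseline HbA1c.

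| Baseline mean, SD | Slope | SD of change | Chi-square | Adjusted | Gain |
|---|---|---|---|---|---|
| 5.8, 0.40 | 1.0 | 0.5 | 61.3% | 68.3% | 7.0 |
| 5.6, 0.40 | 1.0 | 0.5 | 52.9% | 59.1% | 6.2 |
| 5.6, 0.30 | 0.7 | 0.707 | 45.3% | 46.2% | 0.9 |
| 5.7, 0.35 | 0.9 | 0.3 | 66.4% | 75.4% | 9.0 |

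Over the assumed range (mean 5.6 to 5.8%, SD 0.3 to 0.4%, slope 0.7 to 1.0), the gain is about 3 to 7 points at SD 0.5 and about 1 to 5 points at variance 0.5. Five further runs at variance 0.5 gave gains of 1.4 to 4.0 points, for example 48.4% to 52.4% and 45.6% to 47.0%. The last row of the table uses an SD that is not in the plan. The Monte Carlo standard error of a single power figure near 50% is √(0.5 × 0.5 / 3000) = 0.9 points, so the smallest gains mean little.

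**5. Type I error.** With no true difference, the chi-square test rejected in 4.5 to 5.4% of runs and the adjusted risk difference in 4.8 to 5.3%.

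**6. Where the gain shrinks.**
- *Other diagnostic routes.* If a further 4% of participants (assumption) reach NOD by criteria unrelated to baseline HbA1c, gains were 2.2 to 2.9 points in runs at variance 0.5. At SD 0.5 they were 3.9 points in one run and about 5 (54% to 59%) in another.
- *Small effect.* At a relative risk near 1.1, power moved from 7.3% to 8.0%, 6.7% to 7.5% and 6.0% to 6.4%, which is 0.7, 0.8 and 0.4 points.

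**The case against.** The strongest reply is that nothing here is an error. A chi-square test on a randomised binary endpoint is valid. The sentence is a general rule that does not name NOD, the article is condensed, and covariates for a secondary endpoint are often left to the analysis plan. HbA1c, the endpoint that the trial is powered for, already gets baseline adjustment. The simulated endpoint is also simpler than the real one: NOD may be diagnosed by glucose or medication and is followed through visits, records and telephone contact. Finally, 11.7% v 19.4% in the first simulated scenario is a relative risk of 19.4 / 11.7 = 1.66, while the Background cites a 10–12% increase for statins.

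Most of this stands as a limit on size. The 10–12% figure describes statin treatment in general, and the Background says that risk is higher with intensive regimens and in people already at risk. It is therefore not a forecast for this comparison, but it does show that a small effect is possible. The adjusted analysis also adds some dependence on a model, and the plan names SPSS 22.0 for all analyses; whether that version can produce the standardised risk difference with its interval was not checked.

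What does not stand is that the matter is simply left open. The article states a test for categorical data, confines baseline adjustment to changes, and gives nothing else for NOD.

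A reader might infer that the chi-square comparison is biased or has the wrong error rate. The documents do not support that: allocation is random and the null rejection rate is about 5%.

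**Conclusion.** The point holds as a minor loss of efficiency. The stated method for NOD ignores a baseline measurement that everyone has and that predicts the outcome. With a 0.2-point difference, adjustment is worth about 1 to 5 points of power if 0.5 is the variance of change and about 3 to 7 if it is the SD. It is worth less when diabetes is diagnosed by routes loosely tied to baseline HbA1c, and about one point or less for a small true effect. These figures rest on an assumed baseline mean, spread and slope, and on NOD counted by month-24 HbA1c.

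Two stronger readings should be resisted. One is that adjustment would cure the low power for NOD: at variance 0.5, power stays near 50% even with a 0.2-point difference. The other is that it removes the effect of a chance difference in baseline HbA1c: it reduces that effect, to the extent that the model describes the relation well.

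**What to change.** In Statistical analyses, pre-specify that the between-arm comparison of NOD is a logistic regression on treatment and baseline HbA1c as a continuous covariate, reported as the standardised (marginal) risk difference with its 95% CI. The standardised difference is preferable to the adjusted odds ratio because it keeps a comparison of overall risk between the arms. Baseline fasting glucose may be added if that is fixed at the same time. Keep the raw counts and percentages per arm, with the chi-square test if wished, as description. Allow additional software if SPSS 22.0 cannot produce the estimate.

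The cost is a sentence or two of wording and minor programming, with no new data, visits or patients. Because treatment is open-label, the change should be made before outcomes are compared by arm.

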### Measurements

Data on the patients’ medical history, physical examination findings, vital signs, anthropometric measures, blood biochemical tests, and imaging parameters will be collected by trained staff at our institution. Weight and height will be measured by trained nurses, and body mass index will be calculated as the weight in kilograms divided by height in meters squared. Body composition will be assessed using a multifrequency bioimpedance analyzer (InBody 720; InBody, Seoul, Korea) [22].

The primary endpoint of this study is the change in hemoglobin A1c after 24 months of statin treatment. The secondary endpoints include changes in other laboratory variables, such as insulin, C-peptide, the insulin resistance index of the homeostasis model assessment, the insulin secretory ability index of the homeostasis model assessment, lipid profiles (including total cholesterol, triglycerides, high-density lipoprotein cholesterol, and low-density lipoprotein cholesterol), adiponectin, C-reactive peptide, and troponin I, after 24 months of statin treatment. Carotid ultrasound and echocardiography will be performed at baseline and after 12 and 24 months of therapy to obtain data on carotid elasticity and cardiac function, respectively. Specifically, the carotid elasticity metrics, including strain, stiffness, and distensibility by the B-mode and speckle-tracking methods, will be measured as described previously [23]. The imaging parameters of cardiac function to be measured include the left ventricular global longitudinal strain by speckle-tracking echocardiography as well as traditional indices derived from two-dimensional, Doppler, and tissue Doppler echocardiography [24]. Additional file 2 provides a detailed description of the methods that will be used to measure the carotid ultrasound and echocardiographic parameters.

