### Sample size

The sample size was calculated by assuming an expected difference of 0.2% in hemoglobin A1c change between the groups and a population variance of 0.5%, based on previous studies [25, 26]. Thus, with a power of 95%, a two-tailed α of 5%, and a presumed dropout rate of 10%, a sample of 250 patients in each group will be sufficient to detect this difference. Accordingly, a total of 500 participants will be randomized and included in our analysis.

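### Two tests are prescribed for the primary HbA1c comparison, and the plan does not say which one decides the trial

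*Protocol article*

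**What the plan says.** Under Measurements the protocol article names one primary endpoint: "The primary endpoint of this study is the change in hemoglobin A1c after 24 months of statin treatment". Under Statistical analyses it gives the method for all change endpoints, this one included: "The difference in changes between the groups will be analyzed using both Student’s *t* test and analysis of covariance to adjust for the baseline values". The only significance rule there is "Two-sided *p* values < 0.05 will be considered statistically significant".

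Three other places could have settled the matter and do not:

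- "The main analyses will be performed on an intention-to-treat basis" chooses the analysis population, not the test.
- The Sample size section states the difference, variability, power and alpha, but does not say which test the calculation is for.
- Strengths and weaknesses adds a further adjusted analysis if certain antihypertensive drugs turn out to be unevenly distributed. It does not rank the two tests either.

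**The concern.** A t test on change and a baseline-adjusted ANCOVA give different estimates, standard errors and p values on the same data. They differ most when the arms differ by chance in baseline HbA1c, because the change-score comparison carries that imbalance into the estimate and ANCOVA corrects for it. One p value may then fall below 0.05 and the other above it.

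The plan does not say what the trial concludes in that case. If success may be claimed on either test, the 5% error rate used in the sample-size statement is not protected. If the choice is made once both p values are known, the conclusion depends on a decision that should have been fixed beforehand.

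**Working it through.** **Inputs from the protocol article.** Two tests of one comparison, each at two-sided 0.05; a difference of 0.2; "a population variance of 0.5%, based on previous studies"; 250 per arm with 10% dropout, so 250 × 0.9 = 225 completers per arm.

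**Assumed, because the document does not give them.** The correlation ρ between baseline and 24-month HbA1c, taken from 0.3 to 0.9, and the ratio s of follow-up SD to baseline SD, taken as 1.0, 1.2 and 1.3.

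**Step 1: the plan's own 5%.** One test alone at |Z| > 1.96 gives 5.0%. In simulations with 225 per arm (40,000 runs at each of ρ = 0.5, 0.7 and 0.8), each test alone rejected in 4.9% to 5.2% of runs. Either test is valid if it is the only one that counts.

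**Step 2: how closely the tests agree.** With baseline SD 1 and follow-up SD s:

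- variance of change: 1 + s² − 2ρs
- residual variance under ANCOVA: s²(1 − ρ²)
- variance ratio, ANCOVA to change score: V = s²(1 − ρ²) / (1 + s² − 2ρs)
- correlation of the two test statistics under the null: √V

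For s = 1 this reduces to V = (1 + ρ)/2. At ρ = 0.5, V = 0.75 and the correlation is 0.866. At s = 1.2 and ρ = 0.7, V = 1.44 × 0.51 / (2.44 − 1.68) = 0.7344 / 0.76 = 0.97.

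**Step 3: type I error under each possible rule.** P(either) is the bivariate-normal probability that at least one |Z| exceeds 1.96. P(both) = 5% + 5% − P(either).

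| ρ | Either, s = 1 | Both, s = 1 | Either, s = 1.2 | Either, s = 1.3 |
|---|---|---|---|---|
| 0.3 | 7.8% | 2.2% | 7.3% | 7.1% |
| 0.5 | 7.3% | 2.7% | 6.7% | 6.4% |
| 0.7 | 6.8% | 3.2% | 5.9% | 5.5% |
| 0.8 | 6.5% | 3.5% | 5.3% | 5.2% |
| 0.9 | 6.0% | 4.0% | 5.7% | 6.3% |

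Simulation of the either rule with s = 1 gave 7.3%, 6.8% and 6.6% at ρ = 0.5, 0.7 and 0.8, in agreement with the table.

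**Step 4: how often the tests would disagree if there is an effect.** With 225 per arm and s = 1, the probability that exactly one test is significant is as follows. The variability is read both as an SD of 0.5 and as a variance of 0.5 (SD 0.707), because the wording allows either.

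| True difference | SD of change | ρ = 0.5 | ρ = 0.7 |
|---|---|---|---|
| 0.2 (planned) | 0.5 | 1% | 1% |
| 0.2 (planned) | 0.707 | 10% | 8% |
| 0.1 (assumed) | 0.5 | 19% | 13% |
| 0.1 (assumed) | 0.707 | 17% | 12% |

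Disagreement is rare if the planned effect holds and the SD is 0.5. It is not rare if the effect is half that size or the variability is larger.

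**The case against.** Four arguments on the other side have force.

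**The either rule is not in the document.** A reader might infer that the trial has an inflated type I error as it stands. The text does not support that: it never says one significant result is enough. A requirement that both be significant fits the wording equally well and gives 2.2% to 4.0% with equal SDs. What stands is that the rule is open. The inflation is conditional on how it is closed.

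**The inflation may be close to nil.** Study participants excludes anyone with HbA1c of 6.5% or more at baseline, while follow-up values are not capped and new-onset diabetes is an outcome. A larger SD at follow-up is therefore plausible, and some combinations then give about 5.2%. Nor should two tests be read as doubling alpha: the 9.75% for independent tests does not apply to statistics correlated at 0.81 or more.

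**ANCOVA is already planned.** One might infer that keeping the t test costs precision, equivalent to 15% to 25% of the sample at ρ of 0.7 to 0.5 with equal SDs. That does not hold, because the t test is reported beside ANCOVA and does not replace it.

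**The open-label design adds little.** The endpoint is a laboratory HbA1c from an accredited laboratory, and the sponsor sees no results before the final analyses are complete. The freedom to choose between two tests would exist in a blinded trial too, once unblinded.

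It can also be said that the decisive model is commonly left to a statistical analysis plan, and that the sentence covers every change endpoint. But the article does not leave the test unstated. It prescribes two for the same comparison at the same threshold, and the primary endpoint is among those covered.

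**Conclusion.** The point holds as an undefined decision rule for the sole primary endpoint. Its size depends on the rule eventually applied:

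- either test may count: about 6.0% to 7.8% with equal SDs, and about 5.2% to 7.3% with a follow-up SD 1.2 to 1.3 times baseline, over correlations of 0.3 to 0.9;
- both must be significant: below 5%;
- one test named in advance: 5.0%.

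These figures rest on an assumed correlation, assumed SDs and a bivariate-normal approximation. ANCOVA is the better choice for the single test: asymptotically it is at least as precise as the change-score t test, and it corrects for chance baseline imbalance. Severity is moderate, because both tests are pre-specified, highly correlated and share the endpoint and main population.

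**What to change.** Add one sentence to the protocol or statistical analysis plan: the single primary analysis is ANCOVA of the 24-month change in HbA1c on treatment and baseline HbA1c in the intention-to-treat population, tested at two-sided 0.05. Add that the unadjusted t test is a sensitivity analysis and cannot decide success, whatever its p value.

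This needs no extra patients, visits or measurements, and no sample-size reduction should be claimed from it. It should be dated before any comparison of outcome data between the arms.

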### Randomization

After the screening phase, randomization will be performed by using a web-based computerized program hosted at the Medical Research Collaborating Center of Seoul National University Hospital. With this program, eligible participants will be randomly allocated in a 1:1 ratio to receive either pitavastatin or atorvastatin. To ensure balance of the treatment groups with respect to gender, a randomization scheme will be performed separately within the stratum of gender. Stratified randomization according to previous use of statins will also be conducted to ensure even distribution of this factor between the study groups.

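### Randomisation is stratified by gender and previous statin use, but no stated analysis includes either factor, so some precision may be lost

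*Protocol article*

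**What the plan says.** The Randomization section sets two stratification factors. For gender, "a randomization scheme will be performed separately within the stratum of gender". For the second factor, "Stratified randomization according to previous use of statins will also be conducted to ensure even distribution of this factor between the study groups". Allocation is 1:1. Block sizes or another restriction within strata are not described.

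The Statistical analyses section describes the comparison of changes in one sentence, which names Student's t test and "analysis of covariance to adjust for the baseline values". Categorical data are compared by the chi-square test. Gender and previous statin use appear in none of these.

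The only other adjustment is under Strengths and weaknesses: "If these covariates are not evenly distributed between study groups despite randomization, we will perform adjusted analysis". It refers to antihypertensive drugs that may affect glucose metabolism, and it depends on an observed imbalance. The same section says that "the influence of previous statin use on the study endpoints cannot be completely excluded" and cites studies suggesting that the "diabetogenic potential of statins might be gender-specific".

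**The concern.** Stratified randomisation with balance inside the strata removes chance differences in those factors from the treatment comparison. A model without the factors still counts the variation they explain as error. The treatment estimate then varies less from trial to trial than its reported standard error implies, so intervals are wider than the design warrants and the test rejects too rarely.

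The conditional adjustment does not close the gap. It concerns other variables. Even if it were extended to the strata, an imbalance would rarely trigger it, because stratification is there to prevent one.

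What is at stake is precision and a little power, for the primary endpoint and for the secondary changes. The protocol gives some reason to care, since it treats both factors as possibly relevant to the endpoints. Because both arms take a statin, a response to statins that differed by gender would appear as a gender effect on change in both arms, which is the variation that a gender term would absorb.

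**Working it through.** The plan states no figure for the contribution of the strata, so there is nothing to reproduce. The check asks how large the loss would be over an assumed range.

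**Inputs**
- Two stratification factors and 1:1 allocation (Randomization).
- ANCOVA on baseline values only (Statistical analyses).
- 250 per group and 10% dropout (Sample size), giving 250 × 0.9 = 225 completers per arm.
- Difference of 0.2 percentage points in HbA1c change, and a variability of 0.5 (Sample size). The article calls the 0.5 a variance. Read literally, the SD is √0.5 = 0.707; if an SD was meant, it is 0.5. Both are shown where it matters.
- R², the share of variance in change explained by the strata after baseline adjustment. It is not given; **assumed 0 to 5%**.
- Balance within strata. It is the stated aim, but the mechanism is not given; **assumed**.

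**Formulas**

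With residual SD σ and n per arm, the model without strata reports SE = σ√(2/n). With the strata balanced, the true SE is σ√(1−R²)·√(2/n). The ratio does not depend on σ or n:
- reported SE / true SE = 1/√(1−R²)
- actual two-sided level = 2·[1 − Φ(1.96/√(1−R²))]

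**Results**

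| Assumed R² | SE ratio | Interval too wide by | Actual level of the 5% test |
|---|---|---|---|
| 0 | 1.000 | 0% | 5.0% |
| 1% | 1/√0.99 = 1.005 | 0.5% | 4.9% |
| 2% | 1/√0.98 = 1.010 | 1.0% | 4.8% |
| 5% | 1/√0.95 = 1.026 | 2.6% | 4.4% |

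**In HbA1c units.** With SD 0.5, the half-width without strata is 1.96 × 0.5 × √(2/225) = 0.0924. With strata it is 0.0919, 0.0915 and 0.0901 at R² of 1%, 2% and 5%. With SD 0.707, the figures at 5% are 0.1307 without strata and 0.1307 × √0.95 = 0.1274 with them.

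**Power at R² = 5%.** Without strata, power = 1 − Φ(1.96 × 1.026 − 0.2/[σ√0.95·√(2/225)]). With strata, the first term is 1.96. With SD 0.707 this gives 85.7% without and 86.8% with; with SD 0.5, 99.0% and 99.2%.

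**Simulation.** 450 completers, permuted blocks of 4 in four strata, SD 0.5, 4,000 replicates per setting. The Monte Carlo error of a 5% rejection rate is √(0.05 × 0.95/4000), or about 0.3 percentage points.

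| R² | Without strata: model SE / empirical SE | Rejected under the null | With strata: model SE / empirical SE | Rejected under the null |
|---|---|---|---|---|
| 0 | 0.0471 / 0.0471 | 4.8% | 0.0471 / 0.0471 | 4.8% |
| 2% | 0.0472 / 0.0469 | 5.1% | 0.0467 / 0.0469 | 5.4% |
| 5% | 0.0472 / 0.0462 | 4.6% | 0.0460 / 0.0461 | 5.1% |

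At 5% the simulation agrees with the formula. At 2% the effect is too small to separate from simulation noise. At 0 the two models coincide, so including the strata costs essentially nothing when they carry no information.

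**The case against.** **An article condenses.** The sentence on ANCOVA does not say that no other covariate will enter, and a full covariate list is often left to the analysis plan, which is not shown. This stands as a limit. The article nevertheless names the tests and what the ANCOVA adjusts for, and that set does not match the randomisation it describes.

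**The loss is conditional.** A reader might infer that the standard errors are too large whatever the data. The documents do not support that. The strata must predict change beyond baseline, and allocation must limit imbalance within strata. The article gives neither an R² nor a block scheme. Under unrestricted randomisation within strata, the nominal level would hold without the strata in the model. This stands.

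**The strata may be weak.** A reader might apply an R² of 10% or 20% and get intervals 5.4% or 11.8% too wide. Nothing in the article supports such values for HbA1c change after baseline adjustment. Strengths and weaknesses offers cautions rather than evidence: it concedes that direct data on gender differences in statin-associated diabetes are lacking, and patients exposed to statins in the preceding month are excluded. Nor does a gender difference in adiponectin level make the loss largest there, because baseline adjustment absorbs much of a difference in level. These objections stand, and are why the range above stops at 5%.

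**Event endpoints.** The calculation is for a linear model and says nothing about the size of any gain for the chi-square comparisons. This also stands.

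**Conclusion.** The mismatch is real: two factors define the randomisation and none of the stated analyses uses them. Its consequence is modest and conditional. With balance within strata and a residual R² of 1% to 5%, intervals are about 0.5% to 2.6% too wide and the 5% test runs at about 4.9% to 4.4%. At the upper end of that range, the power lost is about 1 percentage point if the stated 0.5 is a variance, and about 0.1 to 0.2 points if it is an SD. If the strata do not predict change, nothing is lost.

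A reader might take the omission to make the primary test invalid. It does not: the treatment estimate is not biased, and any departure from the nominal level is conservative. The point is worth acting on because the remedy is nearly free, not because a conclusion is threatened.

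**What to change.** State in the Statistical analyses section, or in the analysis plan before the data are analysed, that the ANCOVA for 24-month change in HbA1c includes treatment, baseline HbA1c, gender and previous statin use (yes/no), the last two as fixed effects with the values recorded at randomisation. Apply the same rule to the ANCOVAs for the secondary changes, each with its own baseline value. The t test has no place for covariates and can stay only as an unadjusted comparison.

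For new-onset diabetes and cardiovascular disease, a comparison stratified by the two factors is reasonable for consistency with the design, with no claim about how much it gains. One added phrase describing how balance within strata is achieved would settle the assumption on which the size of the effect depends.

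The cost is one clause and two model degrees of freedom among about 450 completers. Both variables are needed to randomise, so no new data are required. Fixing them in advance also removes a later choice of whether to adjust for them.
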